## 8.4 Statistical Methods

This section describes the statistical methods that address the primary and secondary objectives of the study. Methods related to exploratory objectives and supportive analyses will be described in a separate document such as Statistical Analysis Plan (SAP).

### 8.4.1 Patient Disposition

The frequency and percentage of patients in each analysis set along with disposition (completed study, early termination, with breakdown for reasons for discontinuation) will be summarized overall and by group (SSC or SSC + KB109).

### 8.4.2 Demographics and Baseline Characteristics

Patient demographics (including age, gender, race, ethnicity, weight, height, and BMI) and baseline characteristics, medical history, and concomitant medications/procedures will be summarized by group either by descriptive statistics or categorical tables. The analysis set will be provided for the Safety and Full Analysis Sets.

### 8.4.3 Analysis of Endpoints of Interest

#### Adverse Events (AEs)

The analysis of AEs will be based on the Safety Analysis Set. AEs will be coded using the most recent version of Medical Dictionary for Regulatory Activities (MedDRA).

A TEAE is defined as any AE starts or worsens in severity on or after the first dose of SP is taken for SSC + KB109 group or on or after the randomization for SSC group. Adverse event summary tables will include all TEAEs, SP-related TEAEs, SAEs, TEAEs by severity, and TEAEs leading to product discontinuation. Summaries will be presented by MedDRA system organ class and preferred term using frequency counts and percentages by group and overall.

The analysis of the following endpoints will be based on the Full Analysis Set unless otherwise specified.

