## **Part 2**

Only patients who have a positive test result for COVID-19 can continue to Part 2 of this study. Part 2 of the study comprises an Intake Period and a Follow-up Period. In Part 2, following confirmation of eligibility criteria, the site will notify an independent, third party vendor that a patient is eligible for randomization no later than 48 hours after a positive test result is received by the patient for COVID-19. Upon randomization (SSC + KB109 or SSC alone), a Kaleido at-home Study Kit (KaSK) and SP (KB109) and dosing instructions (as applicable) will be shipped via overnight delivery to the patient's home. The KaSK will include a thermometer, a pulse oximeter, and telemedicine contact information. Patients should continue to record COVID-19-related symptoms using TrialPace™ until the KaSK is delivered.

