### **Part 2, Intake Period**

The Intake Period (Days 1-14) will begin the morning after receipt of the KaSK. All patients will continue to follow the SSC guidance as provided by the treating healthcare provider throughout study participation. In the Intake Period, all patients will continue to record their daily COVID-19-related symptoms, selected COVID-19 signs, responses to questions related to QOL measures, healthcare utilization measures, and concomitant medications taken in the previous 24 hours using TrialPace™ where appropriate. Patients randomized to SSC + KB109 will begin consuming KB109 on Day 1 after recording the required information. All KB109 usage will be noted in the patient's SP log. For all patients in both groups, temperature and oxygen saturation will be measured and recorded as needed throughout the day prior to taking anti-pyretic medication.

Wellness visits by telephone call between Day 1 and Day 14 will be conducted to follow-up on the patient's health status, to ascertain compliance with SP usage or completion of TrialPace™ questions, and to reeducate the patient on the importance of adherence to study instructions including SP usage (where applicable). When wellness and telemedicine visits fall on the same day, they will be combined as a telemedicine visit.

On Day 14, all patients will undergo a telemedicine visit where the following will be conducted: an abbreviated physical examination, an assessment of safety and other protocol-specified measures of health, and an evaluation of whether follow-up treatment is recommended due to a deterioration of COVID-19 symptoms. Patients in the SSC + KB109 group will stop taking KB109 on Day 14. If feasible blood samples for clinical chemistries, biomarkers and serological measures of immunity, and nasal/oropharyngeal swabs for quantitative viral load assessments (research purposes only), will be collected; sample collection may occur at the patient's home by a healthcare professional, remotely, or at the study site or clinic.

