| Confirm eligibility criteria                                         | X                    |                                             |       |               |               |                |                |                  |                |                |                |                |
| Randomization                                                        | X                    |                                             |       |               |               |                |                |                  |                |                |                |                |
| Consume KB109 for patients in this group (SSC + KB109)                           |                      | X                                           | Daily |               |               |                | X              |                  |                |                |                |                |
| Physical Examination                                                             | X        | X                               |       |               |               |                | X  |                  |                |                | X  | X  |
| Height, weight, BMI calculation                                                  | X                    |                                             |       |               |               |                |                |                  |                |                |                |                |
| Patient-assessed COVID-19 Signs (temperature and oxygen saturation)  | X                    | X                               | Daily |               |               |                | X              |                  | X              | X              | X              | X              |
| Patient-assessed Wellness Check COVID-19 Condition                   | X                    | X                               | Daily |               |               |                |                |                  |                |                |                | X              |

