## **7 ADVERSE EVENT REPORTING**

### **7.1 Definitions of AEs, Period of Observation and Recording of AEs**

For convenience, standard terms language included in ICH guidance relevant to the conduct of clinical trials are used in this protocol. An example of such a term included in this protocol is “treatment-emergent,” included in ICH E9. Use of this standard term is not intended to connote treatment with a medicinal product administered.

An AE is defined as any untoward medical occurrence in a patient involved in a clinical study administered a SP and that does not necessarily have a causal relationship with the product. An AE can, therefore, be any unfavorable and unintended sign (including a clinically significant abnormal laboratory finding which has worsened from baseline), symptom or disease temporally associated with the use of a product, accidents, whether or not considered related to the product or study-related procedure.

All AEs are collected from the time the informed consent is signed until the end of the Follow-up Period. This includes events occurring during the Screening Period of the study, regardless of whether or not SP is administered. Where possible, a diagnosis rather than a list of symptoms should be recorded. If a diagnosis has not been made, then each sign or symptom should be listed individually. All AEs should be captured on the appropriate AE pages in the eCRF and in source documents.

All AEs must be followed to closure (the patient’s health has returned to his/her baseline status or all variables have returned to normal), regardless of whether the patient is still participating in the study. Closure indicates that an outcome is reached, stabilization achieved (the PI does not expect any further improvement or worsening of the event), or the event is otherwise explained. When appropriate, medical tests and examinations are performed so that resolution of event(s) can be documented.

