## 8.3 Analysis Sets

### 8.3.1 Safety Analysis Set

The Safety Analysis Set will include all randomized patients. Patients will be included in the group based on the fact that whether or not they actually consumed any amount of KB109: patients who actually consumed any amount of KB109 will be in the SSC + KB109 group; otherwise patients will be in the SSC alone group.

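### TEAEs are counted from randomization in the SSC group but only from first dose in the SSC + KB109 group, which modestly inflates SSC in the all-TEAE and severity tables

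*Protocol*

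**What the plan says.** Section 8.4.3 (Adverse Events) sets the start of the TEAE window separately for each group: "on or after the first dose of SP is taken for SSC + KB109 group or on or after the randomization for SSC group". The AE tables are counts and percentages by group. They cover all TEAEs, product-related TEAEs, SAEs, TEAEs by severity, and TEAEs leading to discontinuation of the product.

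The timeline comes from Section 4.1 and Table 1. Table 1 places randomization in the Screening column. After randomization the kit and any product "will be shipped via overnight delivery". For both groups, "The Intake Period (Days 1-14) will begin the morning after receipt of the KaSK". For the active group, "Patients randomized to SSC + KB109 will begin consuming KB109 on Day 1 after recording the required information".

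Collection is common to both groups under Section 7.1: "All AEs are collected from the time the informed consent is signed until the end of the Follow-up Period".

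Section 8.3.1 puts all randomized patients in the Safety Analysis Set and groups them by actual intake. Anyone who consumed any KB109 is in SSC + KB109; "otherwise patients will be in the SSC alone group".

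The primary objective (Section 3.1.1) compares safety with SSC alone. The primary endpoint (Section 3.2.1) is the number of patients with product-related TEAEs.

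**The concern.** An event in the days between randomization and first dose is a TEAE for an SSC patient. For an SSC + KB109 patient the same event is collected but is not a TEAE, unless it worsens after dosing begins. Both groups share the same Day 1 and the same planned end of follow-up, so nothing later offsets the unequal start, and the protocol describes no adjustment for time at risk.

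The primary objective is comparative, but relatedness to a product has no natural counterpart in a group that takes none. A reader comparing the groups will therefore turn to the tables of all TEAEs and of TEAEs by severity. Those tables carry a built-in difference that favours KB109. The extra days also fall early in the illness, and under Section 7.3.3 clinically significant worsening of COVID-19 symptoms is recorded as a TEAE or SAE.

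**Working it through.** **The plan's own safety figures.** Table 4 is the only computed safety figure, and it is not in dispute. Exact Clopper-Pearson 95% intervals with the event count rounded to a whole number reproduce all eight rows. For example, 15/148 gives 5.8% to 16.2%, half-width 5.2 points. The evaluable numbers also agree within rounding: 350 × 0.85 = 297.5 (stated 296) and 400 × 0.85 = 340.

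**Length of the gap.** Take randomization as day R. Overnight shipping gives receipt on R + 1. Day 1 and the first dose are the next morning, R + 2. So the gap g is about 2 days. The protocol states no maximum delivery time, and Table 1 allows Day 1 a window of +1 day, so g = 1 to 3 is shown as a range.

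**Length of the windows, for completers.** SSC + KB109 has Day 1 to Day 35, which is 35 days. SSC has 35 + g.
- g = 1: 36 days, 1/35 = +2.9%
- g = 2: 37 days, 2/35 = +5.7%
- g = 3: 38 days, 3/35 = +8.6%

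**Effect on the percentage with a TEAE.** Assume the true risk is the same in both groups. Let p be the 35-day risk and m the event rate in the gap relative to the later average. Then

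SSC percentage = 1 − (1 − p)^(1 + m·g/35).

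With m = 1 (constant rate) and g = 2:
- p = 20%: 1 − 0.80^(37/35) = 21.0%
- p = 40%: 1 − 0.60^(37/35) = 41.7%

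The protocol gives no any-TEAE rate. The values of p below are borrowed from Table 4, where they stand for product-related rates, and are illustrative only.

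| 35-day risk, both groups | SSC, g = 1, m = 1 | SSC, g = 2, m = 1 | SSC, g = 3, m = 1 | SSC, g = 2, m = 3 |
|---|---|---|---|---|
| 10% | 10.3% | 10.5% | 10.8% | 11.6% |
| 20% | 20.5% | 21.0% | 21.5% | 23.0% |
| 40% | 40.9% | 41.7% | 42.6% | 45.0% |
| 60% | 61.0% | 62.0% | 63.0% | 65.8% |

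Over g = 1 to 3 and m = 1 to 3, the false excess in SSC runs from 0.3 to 8.4 points and always has the same sign. The value m = 3 is an assumption; the protocol does not quantify early event rates.

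**Interaction with Section 8.3.1.** A patient randomized to SSC + KB109 who has an event in the gap and never takes a dose moves to SSC. Section 8.4.3 then appears to count that patient's events from randomization, so the event becomes an SSC TEAE. Section 5.5 makes this possible: a patient hospitalized for worsening COVID-19 is discontinued, which can happen before dosing starts. The protocol gives no basis for estimating how many such patients there would be, so no size is attached.

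**With one common origin** (Day 1 in both groups, or randomization in both) the windows are equal and the excess from the gap is 0 points.

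**The case against.** A reader might infer that the primary safety result is biased. The documents do not support that. Section 7.3 judges causality against the study product. SSC patients take none, and an event before the first dose cannot be caused by it, so the extra SSC days should add essentially no product-related TEAEs. Table 4 concerns the same product-related rate and is likewise unaffected.

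A reader might also infer that hospital admissions are distorted. They are a separate secondary endpoint (Section 3.2.2), counted over the Intake and Follow-up Periods, which start at Day 1 in both groups. Section 8.4.3 lists SAEs without limiting them to treatment-emergent ones, and SAEs are collected from consent, so the text does not establish that the SAE table uses the unequal window.

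Several limits on size also stand:
- Symptoms within expected progression are not TEAEs (Section 7.3.3), so only part of any early deterioration counts.
- That events cluster in the gap is plausible in acute illness, but the protocol does not show it.
- At a constant rate and a 2-day gap, the excess of 1.0 point at 20% and 1.7 points at 40% is well below the Table 4 half-widths (6.3 to 6.8 and 7.6 to 8.2 points). AE reporting is descriptive, so no formal test turns on it.
- The figure of 37 against 35 days holds for completers. After early termination, Section 5.5.1 ties AE monitoring to the last product dose, which has no equivalent in SSC.

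None of this removes the point. The asymmetry is written into the protocol, not left open for the SAP. It acts in one direction, and a bias of this kind does not shrink as the sample grows.

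**Conclusion.** The point holds for the tables of all TEAEs and of TEAEs by severity. As written, SSC completers have about 37 days at risk against 35. With equal true risk, a constant event rate and a 2-day gap, SSC would show about 1.0 point too many at a 20% rate and 1.7 points at 40%. The excess would be 3.0 and 5.0 points if the event rate in the gap were three times the later average. The rates and the multiplier are assumptions; the direction is not, since the extra days can only add patients with events to SSC. The reassignment of never-dosed patients in Section 8.3.1 pushes the same way by an unknown amount.

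The effect is modest, but it favours the product in the comparison that the primary objective calls for, and it is easily avoided. This should be fixed; it does not undermine the primary endpoint.

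**What to change.** In Section 8.4.3, use one origin for both groups: a TEAE is an AE that starts or worsens on or after Day 1, the morning after kit receipt, through the end of Follow-up. Applying Day 1 as a calendar day, whatever the time or date of the first dose, avoids a leftover difference within Day 1 or when dosing starts late.

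Tabulate AEs between randomization and Day 1 separately, by randomized group. Put all AEs of patients who never reach Day 1 in that table. Those patients then have a defined status, and pre-Day 1 events of never-dosed KB109 patients are not counted as SSC TEAEs. Patients who reach Day 1 but never dose would still sit in SSC under Section 8.3.1; a footnote giving their number and their events is enough.

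Starting at randomization in both groups would also equalize the windows, but events before dosing in never-dosed KB109 patients would still fall in SSC.

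The cost is a short edit and one extra table. AEs are already collected from consent and Day 1 is already defined for both groups, so no new data are needed. The change is best made before the interim analysis.

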#### Time to resolution of overall 13 COVID-19 related symptoms and the 8 cardinal COVID-19 related symptoms

The Kaplan-Meier method will be used to estimate median time to resolution and resolution rate specific to each group. Kaplan-Meier graphs will be generated; quartiles and point probabilities will be calculated. Interval estimates will be calculated using 95% point-wise CIs.

Proportion of patients with reduction from Baseline (symptom present at Baseline) and proportion of patients with symptom becomes absent (symptom present at Baseline) at EOI and Follow-up for each of 13 individual COVID-19 related symptom will be summarized by group using frequencies and percentages.

#### Change from Baseline to EOI in overall composite scores of the 13 COVID-19 related symptoms and the 8 cardinal COVID-19 related symptoms

Baseline is calculated as the average of non-missing measurements on Day -2, -1 and 1 (before first dose of KB109), and the EOI will be calculated as the average of non-missing measurements on Day 12, 13 and 14. These measurements will be analyzed using analysis of covariance (ANCOVA) model. In this model, the response variable is the change from Baseline to EOI measure, and the model will include factors for group, visit (Day 2-4, Day 5-11, and Day 12-14), the interaction of group by visit, site, age group ( $\geq 18$  to  $<45$  years,  $\geq 45$  to  $<65$  years,  $\geq 65$  years), and comorbidity status (Yes, No); and the Baseline value. Average of non-missing measures from multiple days will be used at each visit. The least-squares mean (LSM) change from Baseline with the associated standard errors will be displayed for each group. Estimated group differences ( $[\text{SSC} + \text{KB109}] - [\text{SSC}]$ ) along with corresponding 95% confidence intervals (CIs) will also be presented for SSC + KB109 group. In addition, the mean of the overall composite score will be presented by group and by visit.

#### Time to resolution of fever

The Kaplan-Meier method will be used to estimate median time to resolution of fever and resolution rate specific to each group. Kaplan-Meier graphs will be generated; quartiles and point probabilities will be calculated. Interval estimates will be calculated using 95% point-wise CIs.

Proportion of patients with oxygen saturation <95% (or <98%) on Day 14 and Day 35, and proportion of patients experiencing hospital admissions during the Intake Period and Follow-up Period will be summarized by group using frequencies and percentages.

Measures collected from the Healthcare Provider Wellness Visits and Healthcare Utilizations during the Intake Period and Follow-up Period will be summarized by group based on the Safety Analysis Set using the following descriptive statistics: sample size, mean, standard deviation, median, minimum value, and maximum value or using frequencies and percentages.

Further details of the model specification, assumptions, and SAS implementation codes will be provided in the SAP.

### **8.4.4 Subgroup Analyses**

Analysis for the secondary endpoint of time to resolution of overall 13 COVID-19 related symptoms and time to resolution of overall 8 cardinal COVID-19 related symptoms, change from Baseline to EOI in overall composite score of 13 COVID-19 related symptoms and overall composite score of the 8 cardinal COVID-19-related symptoms will be conducted for the following subgroups based on the Full Analysis Set:

- Study site/center
- Age group ( $\geq 18$  to  $< 45$  years,  $\geq 45$  to  $< 65$  years,  $\geq 65$  years)
- Comorbidity status (Yes, No)
- Baseline BMI subgroup ( $< 30$  kg/m^2,  $\geq 30$  kg/m^2)
- Ethnicity (Hispanic or Latino, Not Hispanic or Latino)

The Kaplan-Meier method will be used to estimate median time to resolution and resolution rate specific to each group for each subgroup. A similar ANCOVA model as the analysis of change from Baseline to EOI in overall composite score of 13 COVID-19 related symptoms and overall composite score of the 8 cardinal COVID-19 related symptoms will be performed. For each subgroup, summary statistics including mean, SD, and 95% CIs will be provided for each group.

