| 8.4.4 Subgroup Analyses                                                                                            | Baseline BMI subgroup and Ethnicity were added. Methodology was also updated.                                                                                                                                                                                                                                  | To identify if there are any differences in the role of the MMT in these subgroups.                                                                                                                                                                                                                                                                                                                                             |
| 8.4.6 Interim Analysis                                                                                             | Added a planned interim analysis                                                                                                                                                                                                                                                                               | As large parts of the study are conducted remotely, an interim analysis to assess whether there are indications that require changes in the conduct of the study will be performed.                                                                                                                                                                                                                                             |

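### The subgroup section is meant to show whether the effect differs between subgroups, but its stated method never contrasts the arm difference between subgroup levels

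*Protocol*

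**What the plan says.** Section 8.4.4 takes four secondary endpoints in the Full Analysis Set: time to resolution of the 13 symptoms and of the 8 cardinal symptoms, and change from Baseline to EOI in the two matching composite scores. It analyses them by five factors: "Study site/center", age group (three levels), "Comorbidity status (Yes, No)", "Baseline BMI subgroup" (cut at 30 kg/m²) and "Ethnicity (Hispanic or Latino, Not Hispanic or Latino)".

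Three outputs are stated:

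- For the two time-to-resolution endpoints, Kaplan-Meier is used to "estimate median time to resolution and resolution rate specific to each group for each subgroup".
- For the two change scores, an ANCOVA similar to the main one is performed.
- Finally, "For each subgroup, summary statistics including mean, SD, and 95% CIs will be provided for each group".

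The main ANCOVA in section 8.4.3 has one interaction, group by visit. It reports the difference between SSC + KB109 and SSC with a 95% CI. Neither section names a group-by-subgroup term or a contrast between subgroup levels.

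Table 5 in the appendix, which explains the version 4.0 changes, gives the reason for adding BMI and ethnicity: "To identify if there are any differences in the role of the MMT in these subgroups". The protocol does not define MMT. I read it as the study product.

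**The concern.** Asking whether the product's role differs between BMI or ethnicity groups is asking about effect modification. The quantity that answers it is the difference between two arm differences, with its own interval. Section 8.4.4 goes beyond listing subgroups, since it fixes the model type and the output, and that quantity is not in it.

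A reader left with results side by side will compare them by eye. The usual shortcut is to note that the interval excludes zero in one level and not in the other, and to infer that the effect differs. That inference is unsound even when the effect is the same in everyone, because each level holds only part of the sample and smaller levels miss the effect more often. At stake is how secondary results are interpreted; the primary safety objective is not affected.

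Site has a problem of its own. The number of sites is not given. If the main ANCOVA were rerun within a single site, its site factor would be constant, and the site strata could be very small.

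**Working it through.** **Inputs from the protocol.** Section 8.1 gives 350 to 400 enrolled and 15% attrition. Section 6.10 gives 1:1 allocation.

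**The plan's own figures.** 350 × 0.85 = 297.5, or 148.75 per arm (stated as 148). 400 × 0.85 = 340, or 170 per arm. Exact Clopper-Pearson intervals reproduce all eight rows of Table 4. The protocol gives no precision figure for any subgroup or change score.

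**Assumptions not in the protocol.** Outcome in SD units; a 60/40 split for a two-level factor; a uniform true effect of 0.2, 0.3 or 0.4 SD; normal approximation without covariate gain.

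**Step 1, precision within a level.** With m patients per arm in the level, the 95% half-width of the arm difference is 1.96 × √(2/m).

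| Share of sample | m per arm (148 / 170) | Half-width in SD (148 / 170) |
|---|---|---|
| 100% | 148 / 170 | 0.23 / 0.21 |
| 50% | 74 / 85 | 0.32 / 0.30 |
| 20% | 29.6 / 34 | 0.51 / 0.48 |
| 10% | 14.8 / 17 | 0.72 / 0.67 |

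**Step 2, chance of discordant levels under one uniform effect d.** In each level, the probability p that the interval excludes zero is about Φ(d/√(2/m) − 1.96). The levels are independent, so discordance is p₁(1 − p₂) + p₂(1 − p₁).

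For 148 per arm, m = 88.8 and 59.2, with standard errors 0.150 and 0.184:

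- d = 0.2: p = 0.266 and 0.193; discordance 0.266 × 0.807 + 0.193 × 0.734 = 0.36.
- d = 0.3: p = 0.516 and 0.372; discordance 0.516 × 0.628 + 0.372 × 0.484 = 0.50.
- d = 0.4: p = 0.760 and 0.586; discordance 0.760 × 0.414 + 0.586 × 0.240 = 0.46.

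For 170 per arm, m = 102 and 68, and the same formula gives 0.39, 0.51 and 0.41. Simulations under the same shares gave 35-52%. In those simulations the interaction interval excluded zero in about 4-6% of trials per factor, the rate expected when the effect does not differ.

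**Step 3, no effect at all.** Leaving site out, there are 3 + 2 + 2 + 2 = 9 levels. Simulation with assumed shares (age 55/35/10%, 40% in the smaller level of each two-level factor) found at least one within-level interval for the arm difference excluding zero in about 30% of trials for one composite. For both composites, with an assumed correlation of 0.8, it was about 41-44%.

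**Step 4, precision of the missing contrast.** For two levels with m₁ and m₂ per arm, the 95% half-width is 1.96 × √(2/m₁ + 2/m₂).

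- 50/50 split: 1.96 × √(2/74 + 2/74) = 0.46 SD at 148 per arm; 0.43 at 170.
- 80/20 split: 1.96 × √(2/118.4 + 2/29.6) = 0.57 SD at 148 per arm; 0.53 at 170.

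The contrast is thus about twice as wide as the overall arm difference (0.21 to 0.23 SD), or more.

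**The case against.** The case against is substantial, and most of it stands.

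- **The SAP may settle this.** Sections 8, 8.4 and 8.4.3 leave statistical detail, supportive analyses and model specification to it, and an interaction term could be added there. The absence of an exploratory label or a multiplicity caveat from the protocol is therefore no error in itself. What remains is that 8.4.4 does state a method and an output, and these do not fit the reason given for the added subgroups.
- **A reader might infer that only per-arm summaries will be reported.** That is not supported for the two change scores. The subgroup ANCOVA follows a model that reports the arm difference with a 95% CI, so within-subgroup differences are implied. Per-arm-only output fits the two Kaplan-Meier endpoints, but the main Kaplan-Meier analyses in 8.4.3 are per-arm too, so this is not a defect of the subgroup section.
- **A reader might infer an inflated type I error.** The version 2.0 change log says the study tests no hypothesis and is not designed to show efficacy. No alpha or p-value is planned, so the percentages above describe how intervals would look, not a breached error rate.
- **Separate models per subgroup are an inference.** Section 8.4.4 does not say that the ANCOVA is fitted separately in each level, nor that site stays in a per-site model.
- **The stated purpose is narrow.** It appears in one rationale entry and covers BMI and ethnicity only.
- **The arithmetic is generic.** The shares and effect sizes are assumed, and similar figures would arise in many trials with as many subgroup levels.

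**Conclusion.** The point holds as a low-severity improvement. The protocol says BMI and ethnicity were added to look for differences between subgroups, and the method it states does not estimate such a difference for any factor. Under a uniform effect of 0.2 to 0.4 SD, a 60/40 split and the planned evaluable numbers, discordant levels would appear in about 35-50% of trials for a given two-level factor. Apparent subgroup differences by chance are therefore likely, though not certain. The figure depends on the assumed split and effect. The gap between purpose and output does not.

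The documents do not support saying that the analyses are confirmatory, that error control has failed, or that false subgroup claims will be made.

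**What to change.** In section 8.4.4, or in the SAP with a reference from it:

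- For the two composite change scores, fit one model in the whole Full Analysis Set for each of age group, comorbidity, BMI and ethnicity, with group-by-subgroup terms. The main model has group-by-visit terms, so let the subgroup terms vary by visit and estimate them at the EOI visit.
- Report the arm difference with 95% CI in each level, and the interaction contrast with 95% CI. For age, with three levels, give the contrasts between levels.
- State that any remark on a subgroup difference rests on that contrast and is read descriptively, because the study tests no hypothesis.
- Summarise site descriptively, without per-site models.

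The cost is a few sentences and a few extra model runs on data already collected. The downside is that contrasts of roughly ±0.43 to 0.57 SD (for 50/50 to 80/20 splits) will allow few statements about subgroups. That reflects how little the sample can say on the question.
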